#### Intervention

Participants will be invited to watch ten episodes of video content on specific target areas of adaptive social emotional mindsets and skill (gender equity, teamwork, curiosity, growth mindset, persistence, purpose, utu, empathy & resilience, social responsibility & cooperation, and generosity) designed specifically for very young adolescents in Tanzania. These videos are produced by Ubongo Kids, a Tanzania-based organization that develops engaging and locally relevant digital content for children in Africa. Ubongo Kids' *edutainment* (a combination of educational and entertainment content) is disseminated via TV and radio episodes to over 6.4 million East African households weekly. Episodes developed for this study will be aired on national television channel, Tanzania Broadcasting Corporation (TBC) every Saturday. Repeat episodes for each social emotional mindset and skill episode will be aired every Wednesday of each week. Episodes will run for an average of 15–10 min each. *Discover Learning* participants will be provided paper-form worksheets that will include: (1) individual activities, (2) peer/sibling activities, and (3) parent/caregiver activities that complement the Ubongo Kids episodes. Participants will be asked to complete short experiential learning activities individually, or with a peer/sibling or adult after viewing the corresponding Ubongo Kids episode. Reflective learning responses to activities will be submitted via paper-based worksheets to *Discover Learning* research assistants. In order to provide motivation to complete the activities and adhere to the intervention content, participants will receive feedback on reflective responses through receipt of responses from program assistants to reinforce and clarify comprehension. Participants will also receive reward stickers pasted to participant worksheets to signify achievements. Parents/caregivers of participating adolescents will receive reminders to their phones through USSD on when to expect a new television or radio episode, and when reflective responses will be collected by research assistants. Midweek, participants and their families will be kept engaged through booster activities and short, informative public health messaging sent to their phones such as tips and practices on hygiene and self-care.

#### Smartphone-Based Intervention Group (Nested Study)

A nested study will be conducted with participants who have access to a smartphone and consistently use WhatsApp Messaging Application (WhatsApp), to assess the effectiveness of using mobile-based technology to implement the intervention. Sixty participants within the intervention group, and who use WhatsApp, will be invited to watch the same ten episodes of Ubongo Kids as the larger study, however, after each episode, experiential learning activities will be sent to this nested sample using WhatsApp instead of provision of paper-based worksheets. VYAs will be asked to complete these activities individually, with a peer/sibling or adult. Responses to activities will be submitted via pre-programmed short, quick chat sessions from the participants to the server as illustrated in Figure 2. Reflective responses will include multimedia material such as short audios, videos or pictures collected by VYAs. WhatsApp will enable youth to receive immediate feedback on their submissions via pre-programmed chat messages. Affirmative words and emojis/images such as congratulations, well done etc. will be sent to participants to reward completion of activities. Throughout the intervention, participants will receive reminders of upcoming episodes and short public health messages delivered via WhatsApp. Parent/caregiver-VYA dyads will receive honoraria in the form of internet data credits worth 1.72 USD upon completion of each week's activities. Figure 3 illustrates the study design, intervention components and anticipated timeline.

**Figure 2 F2:**
[figure not shown]
Screenshots of chat messages sent to participants in mobile-based group.

**Figure 3 F3:**
[figure not shown]
Timeline of study.

### Recruitment and Eligibility for Study

#### Youth

Study participants will include adolescents ages 10–14 recruited from four public primary schools in Temeke District, Dar es salaam. The study will leverage the relationship that the local implementation partner, Health for a Prosperous Nation has with the school district in order to gain access to the schools. The schools will be selected if they meet the following criteria: (1) have a population of more than 180 students aged 10–14 years, (2) socio-demographic status is typical of public schools in the area, (3) is a government-run public school, and (4) is not a boarding school. Schools will be excluded from the study if students attending the school have taken part in any behavior change intervention within the last 7 years and/or if the school has additional classes or programs after school. The eligibility criteria for study participants will include: (1) Must be a 10–14 years of age enrolled in 3rd to 6th grades in the four selected schools, (2) Adolescent has provided verbal assent to participate (3) Adolescent's parent/caregiver has provided written consent for participation in the study, (4) Parent/caregiver has access to a phone with USSD or WhatsApp capability (for the nested study); and (5) Adolescents must have access to television that broadcasts the TBC channel.

#### Parents/Caregivers

Parents or caregivers of adolescents participating in the intervention and who consent to participate in the study will be invited to complete a survey at baseline and endline. Parents and caregivers will agree to participate in the parent/caregiver-youth activities. Midweek, participating parents/caregivers and their families will be engaged through short, informative messaging sent to their phones such as tips and practices that support learning content and reminders on upcoming episodes.

### Sample

Based on the average population of each school, a cluster size of 100 will be required per school to detect a minimum detectable effect of 0.484 and a statistical power of 80% at a confidence level α = 0.05 for a two-tailed *t*-test (45). Assuming a participant dropout rate of 11.25% from the *Discover Learning* pilot study conducted in 2017 the final sample size will include 500 participants. The nested study will include all participants who have access to a smartphone with WhatsApp functionality. The study will be reported according to CONSORT guidelines.

### Study Instruments

This study will employ a mixed methods design to assess the impact of *Discover Learning* on participant social emotional mindsets and skills, gender norms, beliefs and behaviors and health and well-being outcomes. Quantitative data will be collected using sequential surveys administered to adolescents and their parents/caregivers at baseline and endline. Qualitative data will be collected at endline through in-depth interviews with adolescents and parents/caregivers, and key informant interviews with teachers. All surveys were pretested by trained researchers in the study setting.

#### Quantitative Data

##### Pre-Intervention Survey

The pre-intervention survey will include a 29-question survey to understand household social and demographic characteristics, phone usage, access to television and engagement with siblings/adults in the family. The survey will be delivered to all parents/caregivers of study participants. Surveys will be sent via USSD or WhatsApp and will take 10–15 min to complete. The results of the baseline survey will be to inform additional technological support required by study participants.

##### Baseline and Endline Survey

The adolescent survey will be administered at baseline and endline to measure changes in social emotional learning and health and well-being outcomes. The survey also seeks to capture changes in gender norms, beliefs and behaviors and positive attitudes toward technology as a learning tool. Measures are included to identify involvement of siblings, parents/caregivers and extended family in the intervention modules and seeks to identify which components of the intervention hold the greatest promise for innovation, scale, and adaptation. The survey questions are adapted from various validated measurement scales and modified to suit the study context and target group. One area of focus for this survey is the testing of a contextually relevant principle of *Utu*, an African philosophy of altruism, kindness, compassion and empathy. A summary of all measures included in the survey are listed in Table 1. The VYA survey will be administered by researchers via a phone call or sent via WhatsApp to participants in the nested study group, and will take 45–60 min to complete.

**Table 1 T1:** Summary of measures to be tested in the *Discover*.

**Primary outcome**	**Validated measurement scale**
**Social Emotional Mindsets**	
Growth mindset	Yeager Growth Mindset (46)
Purpose	The Dimensions of Identity Development Scale (47)
Goal orientation	The Goal Orientation and Learning Strategies Survey (48)
Curiosity	The Trait State Curiosity Scale (49)
Persistence	The Scale for Measuring Persistence in Children (50)
Utu^1^	Measure Scale for Ubuntu (51); and Compassionate Engagement and Action Scale (52)
Social responsibility and cooperation	Teamwork and Collaboration Assessment for High School Students (53)
Persistence	The Scale for Measuring Persistence in Children (50)
Adverse life experiences	Adverse Childhood Experiences Questionnaire (ACE) (54)
**Social Emotional Skills**	
Teamwork	Teamwork and Collaboration Assessment for High School Students (53)
Empathy	The Empathy Questionnaire for Children and Adolescents (EmQue-CA) (55)
Gender equity	Gender Attitudes Scale - Choices curriculum (56)
Generosity	The Interpersonal Generosity Scale (57)
Resilience	Child & Youth Resilience Measure-Revised (CYRM-R) (58)
Coping skills	Spirito KIDCOPE checklist (59)

1 *Utu refers to is a traditional African philosophy, defined as communicating, caring, and sharing with humans in harmony with all of creation*.

##### Parent Survey

The parent survey contains questions on demographic socio-economic characteristics of households. Questions from the Simple Tanzania Poverty Scorecard (60) are adapted to determine how many participating households live below the national poverty line. A gender norm, beliefs and behaviors measure is included in the parent survey to capture changes in from baseline to endline in parents/caregivers. Evidence from both the pilot and first round of implementation of Discover Learning indicated that parental/caregiver gender norms, beliefs and behaviors did change after participation in Discover Learning. Including a measure of gender norms, beliefs and behaviors will allow the current study to capture these changes.

##### Discrete Choice Experiment (DCE)

A discrete choice experiment is included after completion of the VYA survey. The DCE provides adolescent participants with eight vignettes that represent different scenarios to elicit individual preferences and decision making pertaining to gender norms, beliefs and behaviors. The DCE will assess youth gender norms, beliefs and behaviors related to each of the ten learning modules. Following each vignette, participants choose from a set of cartoon images of either boys only, girls only, or boys and girls to respond to the illustrated vignette (61). All scenarios and images will be uploaded and presented digitally to participants.

#### Qualitative Data

Qualitative data will be collected in the form of in-depth interviews administered to participants, their parents/caregivers and teachers. Adolescents and their parents/caregivers will be invited to participate in a semi-structured in-depth interview after the completion of the intervention. Each interview will last no more than an hour and will provide information on respondent's experience with the intervention. Teachers will provide key-informant data to assess how well the intervention complemented in-person instruction.

### Data Collection

For this study, the data collection procedures will ensure minimal physical contact with study participants as a precaution against increasing the risk of transmission of COVID-19. Recruitment activities will start in July 2020. A copy of the announcement script for the study will be sent out to parents. The research team will call and screen parents prior to obtaining consent. If participants meet eligibility criteria, parents will provide verbal consent for their VYA to participate in the intervention. After receiving consent from parents/caregivers, verbal assent will be sought from the study participants to participate in *Discover Learning* and data collection activities. All assent/consent will be conducted in Swahili, the local dialect, by trained researchers in human-subjects research. Data from the pre-intervention and baseline youth and parent surveys will be collected via phone calls and WhatsApp in August and September 2020. Following the 10-week intervention, endline surveys will be administered to VYAs and parents/caregivers. In addition, researchers trained in qualitative methods will administer in-depth interviews over the phone to VYAs and parents/caregivers. All data collection activities are expected to be completed in January 2020. The datasets that will be generated and/or analyzed during this study will not be made publicly available due to the sensitive age of the study participants (10–14-year-old), but may be available from the corresponding author upon reasonable request. All approved IRB and data safety guidelines will be followed prior to providing data.

### Data Analysis

All quantitative data will be cleaned, coded and analyzed in Stata SE 16.0 (62). Statistical analysis will be conducted according to the Intention-To-Treat principle. Participants who do not complete all intervention modules due to attrition or who have missing data will be examined for inclusion in the final analysis. If <2% of the observations contain missing values on each variable and the pattern of missing values is random, then Listwise Deletion method will be used (63). If missing data is not determined to be missing at random, multiple imputation models will be used for analyzing adolescent data (64). All data will be examined for skewness or data non-normality. Multivariate regression models will be used to assess the effect of the intervention on study outcomes and will control for age, gender, socioeconomic status, school and household characteristics. Statistical significance for all analyses will be set at *p* < 0.05. Psychometric analysis of measures including exploratory and confirmatory factor analysis will be used to establish measure validity. Structural equation modeling (SEM) will be used to test structural paths between latent constructs. Potential mediating and modifying variables will be assessed. SEM models will be assessed for goodness of fit using indices including the root mean square error of approximation (RMSEA) (65), the comparative fit index (CFI) (66), the Tucker Lewis Index (TLI) (67) and the standardized root mean residual (SRMR). All qualitative data will be transcribed and translated verbatim from Swahili to English by trained translators. All participant identifiers will be removed from transcripts. All audio recordings of transcripts will be destroyed after transcription is completed and translation have been verified. Translations will be uploaded to Atlas.ti for analysis (68). A grounded theory approach will be used to identify emergent themes (69). The analytical steps will be conducted by two separate analysts. *Line-by-line coding of* each transcript will be used to identify initial codes that capture implicit meanings, and common relationships and significance between codes. Where appropriate codes will be left *in vivo* to preserve participant language and meaning. Next, *focused codes* will be developed from the most significant and/or frequent initial codes to make analytical sense of the data. *Axial coding* will be used to represent the content of focused codes and to connect relationships between codes, categories and concepts. During the application of focused and axial coding, analysts will meet to discuss and revise codes until consensus is reached. Researchers will write memos to capture connections and to construct analytic notes. Researchers will further hold discussions to help identify emergent themes and connections between themes through an iterative deductive process. Exemplar quotes will be selected to illustrate emergent themes. All transcripts will be stored in an access-controlled server that is located safely within the local implementation partner, HPON's Tanzania office and destroyed after 5 years.

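### Read literally, the missing-data rule uses multiple imputation where its assumption fails, has no rule for random missingness of 2% or more, and leaves the ITT analysis set open

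*Protocol article*

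**What the plan says.** All the rules are in the Data Analysis section of the protocol article, in this order:

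- Principle: "Statistical analysis will be conducted according to the Intention-To-Treat principle".
- Analysis set: "Participants who do not complete all intervention modules due to attrition or who have missing data will be examined for inclusion in the final analysis". No criterion for the examination is given.
- First branch: "If <2% of the observations contain missing values on each variable and the pattern of missing values is random, then Listwise Deletion method" is to be used.
- Second branch: "If missing data is not determined to be missing at random, multiple imputation models will be used for analyzing adolescent data".
- Outcome model: multivariate regression that "will control for age, gender, socioeconomic status, school and household characteristics".

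The Sample section sets the amount of loss that the plan expects: "Assuming a participant dropout rate of 11.25% from the" 2017 pilot. It gives a final sample of 500.

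**The concern.** Standard multiple imputation gives valid estimates under MAR. The second branch switches it on when MAR is judged not to hold, and nothing else is named for that case. The first branch is limited to very small losses, which the plan's own dropout figure exceeds. The ordinary situation, a moderate loss that is plausibly MAR, therefore has no stated method. The observed data also cannot tell MAR from data missing not at random (MNAR), so the trigger cannot be operated as worded.

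The inclusion step is a separate fault. Under ITT, failure to complete modules is no ground for leaving a child out. Examining such children case by case, with no criterion, makes the analysis set a decision that can be taken with the data in view.

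At stake is the estimated effect of the intervention. If children who are lost or left out differ from those who stay, in ways the analysis does not account for, the estimate moves away from its value for all enrolled children.

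**Working it through.** **Step 1: planned loss against the 2% limit.** Inputs from the Sample section are 100 per school, four schools, 11.25% dropout and a final sample of 500.

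- The plan's own figure: 4 × 100 = 400. Then 400/(1 − 0.1125) = 450.7, so 451; or 400 × 1.1125 = 445. Neither gives 500, which would correspond to a loss of 1 − 400/500 = 20%. The excess is conservative and does not affect this point.
- Expected loss with 500 enrolled: 500 × 0.1125 = 56 children. The 2% limit is 500 × 0.02 = 10 children. The planned loss is 11.25/2 = 5.6 times the limit.

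If drop-outs have no endline survey, every endline outcome exceeds the limit and listwise deletion is not available.

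**Step 2: which rule applies, read literally.**

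| Missing on a variable | Judged random | Judged not MAR |
|---|---|---|
| under 2% | listwise deletion | multiple imputation |
| 2% or more | no rule | multiple imputation |

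The expected loss puts endline outcomes in the bottom row. One cell of that row is empty, and the other assigns a method whose assumption has just been rejected. The imputation sentence is also confined to adolescent data, although parents are surveyed at baseline and endline too.

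**Step 3: simple size of the bias.** Bias in a mean = missing fraction × gap between missing and observed children. The gaps are assumptions, because the article gives no outcomes for drop-outs.

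- Gap 0.1 SD: 0.1125 × 0.1 = 0.011 SD
- Gap 0.25 SD: 0.1125 × 0.25 = 0.028 SD
- Gap 0.5 SD: 0.1125 × 0.5 = 0.056 SD
- At the 2% limit with gap 0.5 SD: 0.02 × 0.5 = 0.01 SD

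This treats the whole gap as unexplained. Any part explained by baseline scores or covariates is removed by a sound imputation model.

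**Step 4: does the method matter at this loss?** I used a simulation with assumed settings: one group of 500, baseline and endline correlated 0.5, true change zero, about 11% of endline missing, 10 imputations from baseline, 1,000 runs. The table shows bias in mean change, in SD.

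| Mechanism | Complete cases | Multiple imputation |
|---|---|---|
| MCAR | 0.00 | 0.00 |
| MAR (low baseline more often missing) | −0.05 | 0.00 |
| MNAR (low endline more often missing) | +0.05 | +0.08 |

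Imputation removes the bias in the case that the rule leaves empty. It does not do so in the case that the rule assigns to it.

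**Step 5: ITT against the inclusion step.** The first sentence fixes the analysis set by principle. The next makes the inclusion of some enrolled children depend on an examination without criteria. Both cannot govern the same analysis.

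**The case against.** The strongest reply is that the imputation sentence is loosely worded. The sentence before it uses the word random informally, so the authors may have meant data that are not MCAR. The trigger is then conventional, and the remaining gap (MCAR with 2% or more missing) costs precision rather than validity. Alternatively, they may have meant that randomness has not been established. Since MAR can never be established from observed data, imputation would then cover nearly everything outside the first branch, which is close to what is recommended below. Both readings are plausible. Neither is what the sentence says, an analyst could follow the literal rule, and the ITT conflict remains under all of them.

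Three stronger readings are tempting, and the article does not support them.

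- A reader might infer that attrition will bias the result in the intervention's favour. Bias is zero under MCAR, and complete cases erred downward in the MAR scenario above. Nothing in the article says that drop-outs do worse. If the comparison is between groups, only differential loss matters.
- A reader might turn the bias into a false-positive rate. That needs a standard error that the article does not settle. A one-group pre-post test with change SD 1 and no clustering gives 1/√444 = 0.047 SD (500 × 0.8875 = 444 children). The stated minimum detectable effect of 0.484 at 80% power implies 0.484/2.80 = 0.173. A bias of 0.056 SD is 1.2 standard errors on the first and 0.3 on the second, so no rejection rate can be quoted.
- A reader might infer that non-completers will be excluded. The text says only that they will be examined.

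It is also fair that sensitivity analyses and imputation details are often left to an analysis plan that is not shown. Their absence is not the fault here. The fault lies in the rules that are stated.

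**Conclusion.** The point holds as a fault in the stated rules. Taken literally, the imputation trigger is the reverse of the condition under which standard imputation is valid. Random missingness of 2% or more has no rule, while the plan expects 11.25% dropout. The inclusion step conflicts with the ITT sentence before it.

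The consequence is a possible bias, not a demonstrated one. At 11.25% loss it is about 0.01 to 0.06 SD for an assumed gap of 0.1 to 0.5 SD, and zero under MCAR. The simulated MNAR scenario gave up to +0.08 SD under its own assumed settings. The direction is open. These figures assume that dropout means no endline survey and refer to a one-group mean change. A between-group comparison would depend on the difference in loss.

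**What to change.** Reword the Data Analysis section before endline data are examined:

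1. Delete the inclusion step. State that all enrolled children are analysed whatever their module completion.
2. Replace the two-branch trigger with one MAR-based primary analysis at any percentage missing. This can be multiple imputation with baseline scores, school and the planned covariates in the imputation model, or a likelihood-based mixed model.
3. Report a delta-adjusted sensitivity analysis for departures from MAR. Shift imputed endline values over a stated range (for example 0 to −0.5 SD) and report where the conclusion changes.

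The cost is wording and a few extra Stata runs. No new data are needed.

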### Study Design

This protocol describes a study that will be conducted to test the impact of *Discover Learning*, a social emotional learning and identity development intervention for very young adolescents. The study employs an intervention design that leverages the principles of adolescent developmental science to improve early precursors of health inequities. A sample of 10–14 year old adolescents will be selected from four primary schools located in peri-urban areas of Temeke District in Dar es Salaam. Participants enrolled in *Discover Learning* will receive a distance learning intervention or will participate in a nested sub-group that includes additional smartphone-based content.

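### The named covariates leave out the baseline score of the same scale, which costs precision and leaves baseline imbalance in an endline comparison of smartphone and paper groups

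*Protocol article*

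**What the plan says.** The Data Analysis section of the protocol article states that "Multivariate regression models will be used to assess the effect of the intervention on study outcomes" and that these models "will control for age, gender, socioeconomic status, school and household characteristics". That is the whole adjustment set, and no other section adds to it. The section does not define the dependent variable.

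The Baseline and Endline Survey section says "The adolescent survey will be administered at baseline and endline to measure changes in social emotional learning and health and well-being outcomes". The Data Collection section places the baseline round in August and September 2020, before the 10-week intervention. Each child's pre-intervention score is therefore planned to exist.

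On the groups, the Study Design section says that enrolled children "will receive a distance learning intervention or will participate in a nested sub-group that includes additional smartphone-based content". The nested-study section ties membership to phone ownership and habit: "A nested study will be conducted with participants who have access to a smartphone and consistently use WhatsApp Messaging Application". It sets the size with "Sixty participants within the intervention group, and who use WhatsApp, will be invited". No random allocation to the two formats and no untreated group is described.

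**The concern.** A child's own earlier score on a scale is usually the best single predictor of the later score. The article spells out its covariates, so a reader who follows it literally would fit a between-group model without that score. The list is given in the article itself, so this is not a detail left to a separate analysis plan.

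Two things are at stake in the smartphone-versus-paper contrast. The first is precision, because the smaller group has only about 60 children. The second is bias. Families with a smartphone who use WhatsApp regularly may differ from the others at the start. Socioeconomic and household variables can capture such differences only in part, whereas the baseline score measures the starting difference on the outcome itself.

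**Working it through.** **The plan's own figures.** The Sample section states "a cluster size of 100 will be required per school to detect a minimum detectable effect of 0.484", with 80% power, two-sided α = 0.05, 11.25% dropout and a final size of 500. These figures are not for the smartphone-versus-paper contrast, and the stated inputs do not reproduce them. Four schools of 100 give 400, and 400 / (1 − 0.1125) = 451, not 500. Two arms of 100 give a minimum detectable effect (MDE) of 0.396 SD, and two arms of 200 give 0.280. A value of 0.484 appears for two against two schools of 100 if the intracluster correlation is about 0.02, but the article states neither that split nor that correlation. This is a separate matter, and nothing below depends on it.

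**Inputs for the contrast.** Taking 60 of 500 in the nested group leaves 440. After 11.25% dropout, 60 × 0.8875 = 53.25 and 440 × 0.8875 = 390.5, so about 53 against 391. The outcome SD is set to 1. Clustering and the other covariates are ignored. The correlation r is not in the article, so 0.3, 0.5 and 0.7 are assumptions.

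**Without baseline (endline score).** SE = √(1/53 + 1/391) = 0.146. MDE = (1.960 + 0.842) × 0.146 = 0.41 SD.

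**With baseline (analysis of covariance).** The variance is multiplied by 1 − r², so the MDE is 0.410 × √(1 − r²).

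**Change score without baseline as covariate.** The variance is multiplied by 2(1 − r), so the MDE is 0.410 × √(2(1 − r)).

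| Assumed r | 1 − r² | Variance cut v endline-only | MDE with baseline | 2(1 − r) | MDE, change score |
|---|---|---|---|---|---|
| 0.3 | 0.91 | 9% | 0.39 | 1.40 | 0.49 |
| 0.5 | 0.75 | 25% | 0.36 | 1.00 | 0.41 |
| 0.7 | 0.51 | 49% | 0.29 | 0.60 | 0.32 |

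The ordering does not depend on the value chosen. The factor 1 − r² is below 1 for any non-zero r, and 2(1 − r) − (1 − r²) = (1 − r)², which is never negative.

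**Baseline imbalance.** Suppose the groups differ by d at baseline, and that children with equal baseline scores would have equal expected endline scores in either group if the format made no difference. An endline-only model then carries a bias of r × d, and a change-score model one of −(1 − r) × d. For an assumed d of 0.2 SD:

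- endline-only: 0.06, 0.10 and 0.14 SD at r = 0.3, 0.5 and 0.7;
- change score: −0.14, −0.10 and −0.06 SD.

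With 60 against 440 (SE 0.138, before dropout), the endline-only bias makes a nominal 5% test reject a true null about 7%, 11% and 17% of the time.

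**The case against.** **The dependent variable is unstated.** The survey's stated purpose is to measure changes, so a change score is a natural reading, and it does use the baseline data. This stands. One cannot say that the plan ignores the pre-measure. A change score without the baseline covariate is still less precise than analysis of covariance.

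**The overall effect may be a single-group comparison of endline with baseline.** No untreated arm is described. In that analysis baseline is the comparator, and adding it as a covariate is not the remedy. This also stands, and it confines the covariate point to between-group models.

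**A reader might infer that the analysis of overall change is unpaired and its standard errors wrong.** At r = 0.5, treating paired records as independent would inflate the standard error by 1/√(1 − 0.5) = 1.41. The article does not support this reading. The Sample section names a two-tailed t-test without saying whether it is paired, and the Data Analysis section neither describes nor rules out a within-child term.

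**A reader might infer that the whole baseline difference stays in the estimate, or that baseline adjustment would make the contrast unconfounded.** Neither follows. An endline-only model keeps about r × d, less whatever the listed socioeconomic and household variables absorb. With self-selected groups, adjustment leaves unmeasured differences in place. Whether analysis of covariance or a change score is less biased depends on an assumption about how the groups would have developed without a difference in format, and the data cannot settle it.

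**The calculated gains are not those of the planned model.** This is correct. The relevant quantity is the correlation of baseline with endline given the listed covariates, which is unknown. The group sizes are also unsettled: the nested-study section gives sixty, while the Sample section takes in everyone with a WhatsApp-capable smartphone.

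**Conclusion.** The point holds for between-group models, which here means the WhatsApp sub-group against paper worksheets. The article names the covariates and omits the baseline score, although it plans to collect it. Adding it is at least as precise as either an endline-only or a change-score model. It also reduces the imbalance bias of an endline-only model.

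The gain in MDE, from about 0.41 SD to between 0.39 and 0.29 SD, rests on assumed correlations of 0.3 to 0.7, on 53 against 391 completers, and on no clustering and no other covariates. The actual gain will be smaller to the extent that the listed covariates already explain the outcome. The bias figures rest on an assumed imbalance of 0.2 SD. The direction of the precision result does not depend on these values, but its size does. The point does not show that the overall baseline-to-endline analysis is wrong.

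**What to change.** - In the Data Analysis section, state the dependent variable, and add the baseline value of the same scale to the covariate list for every between-group endline model.
- For overall baseline-to-endline change, name a within-child analysis: a paired comparison, or a mixed model with a child random intercept and school as a fixed effect.
- Say that baseline adjustment does not remove confounding by smartphone access, and word the conclusions of the smartphone-versus-paper contrast accordingly.
- Reconcile the two definitions of the nested group, so that the size of the contrast is known.

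This costs a few lines of text. The baseline survey is already planned, so no new data are needed.
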